## Abstract

**Background:**

Extubation failure, defined as reintubation within 48 h, is associated with increased intensive care unit (ICU) length of stay and higher mortality risk. One cause of extubation failure is secretion retention, resulting from an inability to cough effectively. Mechanical insufflation-exsufflation (MI-E) simulates a cough aiding secretion clearance. However, MI-E is not routinely used in the ICU for invasively ventilated patients. This study aims to determine feasibility and acceptability of a randomised controlled trial (RCT) examining MI-E use to promote extubation success in intubated, ventilated adults.

**Methods:**

It is a single-centre, feasibility RCT with semi-structured interviews, economic scoping, and exploratory physiology study.

The feasibility RCT (*n* = 50) will compare standard care to a MI-E protocol including a minimum of two MI-E sessions via the endotracheal tube prior to extubation. Post-extubation, MI-E will be delivered via facemask or mouthpiece up to two times/day for 48 h. MI-E settings will be individualised. All patients will receive standard care (no MI-E) in relation to mechanical ventilation, weaning, rehabilitation, physiotherapy techniques such as positioning, manual airway clearance techniques, manual/ventilator hyperinflation, endotracheal suctioning, and nebulisation. Clinical data collection will occur before, on completion, and 5-min post-physiotherapy sessions (intervention/control arms). Resource use will be calculated for each 24-h period. Analyses will be descriptive and address feasibility outcomes including participant recruitment and attrition, proportion of MI-E treatment sessions completed, dataset completeness, and frequency of adverse events and acceptability.

Semi-structured online interviews informed by the Theoretical Framework of Acceptability (TFA) with patients, clinicians, and family members will explore the acceptability of the MI-E intervention and study processes.

Interview data will be analysed using reflexive thematic analysis based on TFA domains through first-level coding.

The embedded physiology study will use electrical impedance tomography and lung ultrasound to explore lung recruitment and de-recruitment during MI-E in a subset of 5–10 patients.

**Discussion:**

This study will examine feasibility and acceptability of a RCT protocol of MI-E to promote extubation success. Study findings will inform design modification and conduct of a future adequately powered trial. Furthermore, the study will contribute and advance the understanding of MI-E use in critically ill intubated adults.

**Trial registration:**

ISRCTN 24603037; IRAS 303674

**Supplementary Information:**

The online version contains supplementary material available at 10.1186/s40814-023-01362-7.

## Background

Extubation failure is defined as reintubation within 48 h and is associated with increased intensive care unit (ICU) length of stay (LOS) [1] and higher mortality risk [2]. One cause of extubation failure is secretion retention, resulting from an inability to cough effectively [3]. Having an endotracheal tube in place impairs the ability to cough due to abduction of the vocal cords and glottis. As a result, airway clearance strategies are used to aid secretion clearance. Suctioning is used commonly to remove secretions from the endotracheal tube, tracheostomy, or upper airway. This technique however has limited effectiveness in clearing secretions from the lower airways and may cause airway trauma [4, 5].

Mechanical insufflation-exsufflation (MI-E) augments inspiratory and expiratory flow to improve secretion mobilisation, through rapidly alternating positive and negative pressure, approximating a normal cough [6]. A previous randomised controlled trial (RCT) based in Portugal examined MI-E in 75 critically ill adults intubated for > 48 h [7]. Using MI-E, they found reductions in re-intubation rates (48% v 17%), mechanical ventilation duration (mean (SD) 17.8 [6] v 11.7 (3.5) days), and ICU LOS post-extubation (9.8 (6.7) v 3.1 (2.5) days (all *p* < 0.05)). More recent trials have demonstrated the superiority of MI-E compared to other airway clearance techniques on physiologic outcomes including sputum weight, static lung compliance, airway resistance, and work of breathing [8, 9]. Recent studies regarding the safety of MI-E in intubated patients indicate that adverse effects such as barotrauma, desaturation, atelectasis, and haemoptysis are rare and transient [10, 11]. However, to date, there is limited adoption of MI-E in ICU [12–14] and limited empirical evidence on its effectiveness [15]. MI-E may be safe and effective in intubated critically ill adults, but more data are required.

During invasive ventilation, positive pressure breaths are delivered followed by a passive expiration. In contrast, MI-E delivers both positive (insufflation) and negative (exsufflation) pressure breaths. Barotrauma and volutrauma associated with large tidal volumes are well documented, with low volume lung-protective ventilation now standard of care, particularly for patients with acute lung injury [16]. However, de-recruitment of lung units due to small tidal volumes can have an equally adverse impact on oxygenation and effective ventilation, attenuating lung injury [17]. To date, no studies have examined the extent of de-recruitment or other adverse events as a result of a negative pressure exsufflation breath applied during MI-E.

We recently conducted a scoping review [18] including 28 studies to map use of MI-E in invasively ventilated critically ill adults. We found MI-E was predominantly used in ICU patients with prolonged weaning from mechanical ventilation and difficulty with sputum clearance. Study populations did not always reflect the heterogeneous nature of invasively ventilated critically ill adults, with some studies enrolling cohorts limited to neuromuscular disease and spinal cord injury. We identified substantial variation in MI-E device settings, timing, and frequency of use across studies.

The recent scoping review [18] also identified a lack of specific qualitative data pertaining to patient and clinician experience of using MI-E. Information was gained through three survey studies which reported qualitative data from open-ended questions around barriers to MI-E in ICU. A common barrier to MI-E use was a perceived lack of skills and knowledge. There were no studies that included patients’ opinions or experiences of MI-E use.

This variation in how MI-E is used combined with uncertainty in terms of the evidence of effect on patient outcomes such as promoting weaning success, reducing extubation failure and safety, limits the ability to make practice recommendations and warrants further investigation. Therefore, the aim of this study is to determine the feasibility of a RCT of MI-E to promote extubation success for intubated, mechanically ventilated critically ill adults.

Our objectives are to determine trial feasibility based on the following feasibility end points:Ability to recruit and retain the proposed 50 participantsAbility to collect outcome data (including follow up data) and to examine dataset completenessAcceptability of the MI-E intervention from the perspectives of patients, family, and members of the interprofessional team including doctors, nurses, and physiotherapists.

## Methods

The protocol conforms to the SPIRIT (Standard Protocol Items: Recommendations for Interventional Trials) guideline [19] and describes a single-centre, individual parallel group, randomised, feasibility RCT with semi-structured interviews, economic scoping, and the incorporation of an exploratory physiology study. A study flow chart is illustrated in Fig. 1; schedule for enrolment, intervention, and follow-up is shown in Table 1, with associated SPIRIT checklist presented in supplementary information 1.

**Fig. 1 Fig1:**
[figure not shown]
Study flow chart

**Table 1 Tab1:** Schedule for enrolment, intervention, and follow-up

	**Data**	**Timepoint**						
		**Enrollment**	**Baseline**	**Pre-intervention**	**During intervention**	**5 min post intervention**	**Duration of study period**	**6-month follow-up**
**Enrolment**	Eligibility screening	X						
	Consent	X						
	Allocation	X						
**Intervention**	Standard care				X			
	MI-E intervention				X			
**Assessments: baseline demographic outcome**	Demographics (age, gender, predicted body weight, history of lung disease, smoking history)		X					
	Reason for intubation		X					
	Date of hospital and ICU admission		X					
	Date of intubation		X					
	Ventilator settings		X					
	Airway type and size		X					
	APACHE II score		X					
**Assessments: clinical outcomes**	Use of HFOT, NIV, tracheostomy						X	
	Use of physiotherapy interventions				X			
	LUS score			X		X		
	Patient pain/discomfort (CPOT; NRS)			X		X		
	CVS parameters (HR, SBP, DBP)			X		X		
	Ventilator parameters (vent settings, resistance, compliance)			X		X		
	Respiratory parameters (RR, SpO_2_)			X		X		
**Assessments: health economics**	• Resource use (staffing requirements, suction frequency, consumable use, antibiotic use, physiotherapy on-call use) • QoL (EQ-5D-5L)				X			X
**Assessments: safety**	Adverse events				X	X	X	

Abbreviations: *APACHE II* Acute Physiology and Chronic Health Evaluation, *CPOT* Critical Care Pain Observation Tool, *DBP* Diastolic blood pressure, *HFOT* High-flow oxygen therapy, *hr* Heart rate, *ICU* Intensive care unit, *LUS* Lung ultrasound, *NIV* Noninvasive ventilation, *NRS* Numeric rating scale, *SBP* Systolic blood pressure, *RR* Respiratory rate, *SpO2* Peripheral oxygen saturations, *QoL* Quality of life

### Feasibility RCT

The study will be conducted in a 21-bed general adult ICU, within a large UK National Health System (NHS) teaching hospital. The unit has approximately 1250 admissions annually and typically admits adults with any condition except cardiac or neurosurgery

#### Participant identification, recruitment, and allocation

##### Eligibility

A research team member will screen all ICU patients on a daily basis against the study eligibility criteria. Our inclusion criteria comprise the following:Adult (≥ 16 years)Expected to require invasive mechanical ventilation for > 48 hClinician identified pre-extubation problems with secretion management defined as poor/weak cough effort and/or secretion load difficult to clear with usual airway clearance management, i.e. suctioning, manual techniques, and positioning (as assessed by the treating physiotherapy clinical team)Identified as ‘ready to wean or weaning’ by the treating clinical team and on a spontaneous mode of ventilation, for example continuous positive airway pressure (CPAP) or pressure support ventilation (PSV)

Our exclusion criteria comprise the following:Positive end-expiratory pressure (PEEP) > 10 cmH_2_OFraction of inspired oxygen (FiO_2_) > 0.7Hemodynamic/cardiovascular instability as defined as noradrenaline infusion of > 0.25 mg/kg or arrhythmia requiring interventionRecent untreated pneumothorax (current admission with no chest drain in situ)Unable to use MI-E pre-/post extubation (contraindications to facemask use including facial/cranial trauma, recent facial surgery; active upper gastrointestinal bleeding/uncontrolled vomiting; recent upper abdominal/thoracic surgery with at risk anastomosis; acute air trapping, i.e. status asthmaticus)Pre-existing neuromuscular condition affecting respiratory musclesPre-existing use of MI-E in the communityPre-existing permanent tracheostomyTreatment withdrawal expected within 24 h or not expected to surviveRe-admission to ICU following index admission within same hospital episodePrevious participation in the study

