#### Statistics and data analysis

##### Sample size calculation

As this is a feasibility trial, a formal sample size calculation based on statistical power to detect a specified treatment effect size is not appropriate. We have selected a sample size of 50 participants based on measurement of feasibility parameters with adequate precision. The participating ICU admits approximately 1250 patients annually with potentially four to five eligible patients each week (minimum of 200 per year). We anticipate recruiting 50 over a 12-month period would be achievable, with an estimated recruitment rate of 25% and a confidence interval width of 0.12.

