##### Safety reporting

The attending consultant physician is responsible for assessing all adverse reactions and adverse events (AEs) and categorising seriousness, expectedness, and relatedness. A list of events that can be expected during this trial, or within this patient population, can be found below.Accidental extubation during the interventionCardiovascular changes (including but not exclusive to hypo/hypertension, brady/tachycardia, arrhythmias)PneumothoraxSputum plugging during the interventionPulmonary complications such as pneumoniaMinor skin irritations due to electrical impedance tomography electrode patch application.

We will record occurrence of the following during a MI-E treatment and control arm interventions: HR, SBP, and DBP increase/decrease > 20% baseline and requiring intervention, arrhythmia (requiring intervention), pneumothorax, acute desaturation to < 85% or > 10% below baseline and requiring intervention, accidental extubation, and cardiopulmonary arrest.

It is the responsibility of the sponsor, chief investigator, and delegated individuals to ensure that the dignity, rights, safety, and well-being of research participants are given priority at all times, and appropriate action is taken to ensure their safety. The recording and reporting of safety events will be in accordance with good clinical practice (GCP) guidelines and study sponsor’s ‘research safety reporting’ standard operating procedure.

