### Trial status

Recruitment commenced on 11th July 2022. The current protocol version (v2.0) is dated 21st March 2022. Recruitment is estimated to be complete by July 2023.

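### The noradrenaline exclusion limit is printed as a dose per kilogram with no time unit, so the only vasopressor threshold cannot be applied as written

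*Protocol article*

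**What the plan says.** Under Eligibility, one of the 11 exclusion criteria is haemodynamic or cardiovascular instability. It has two limbs: "noradrenaline infusion of > 0.25 mg/kg or arrhythmia requiring" intervention. The first limb carries a number and a mass per kilogram. It gives no per-minute or per-hour term and no period over which a dose would be added up.

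The criteria are meant for repeated use at the bedside: "A research team member will screen all ICU patients on a daily basis against the study eligibility criteria".

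Elsewhere the article offers nothing that would complete the unit:

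- The PEEP exclusion in the same list has its full unit (cmH2O), and the FiO2 exclusion is properly a fraction.
- Table 1 lists heart rate and systolic and diastolic pressure, but no vasopressor dose.
- The haemodynamic limits under Safety reporting are changes during treatment, "HR, SBP, and DBP increase/decrease > 20% baseline and requiring intervention". They are not drug doses and not entry limits.

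Under Trial status the article points to a fuller document: "The current protocol version (v2.0) is dated 21st March 2022".

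**The concern.** A limit on a running infusion has to be expressed as mass per kilogram per unit time. The printed limit has the dimension of a dose, so a screener cannot compare it with a pump rate without supplying something the article does not give.

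The criterion helps decide who is randomised, and so who may receive alternating positive and negative airway pressure. Cardiovascular changes are on the trial's own list of expected events. The limit is also the only restriction on vasopressor support at entry. If the line were carried into a later trial's eligibility text, new sites would face the same ambiguity.

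One feasibility outcome in Table 2, the proportion of eligible patients approached, consented and randomised, has a denominator that depends on the criteria being applicable. It is therefore worth asking whether that estimate could be disturbed.

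**Working it through.** **Inputs from the article.** Limit: 0.25 mg/kg (Eligibility). Eligible pool: "potentially four to five eligible patients each week (minimum of 200 per year" (Sample size calculation). Target and precision: "We anticipate recruiting 50 over a 12-month period would be achievable, with an estimated recruitment rate of 25% and a confidence interval width of 0.12" (same section).

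**Assumptions, not in the article.** A 70 kg patient; infusion rates of 0.05 to 0.5 microg/kg/min; a shift of 2 to 20 patients in the eligible pool. All are for illustration only.

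**1. The literal reading: a cumulative dose.** 0.25 mg/kg = 250 microg/kg. Time to reach it = 250 / (rate × 60) hours.

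| Assumed rate (microg/kg/min) | Hours to reach 0.25 mg/kg |
|---|---|
| 0.05 | 83.3 |
| 0.1 | 41.7 |
| 0.25 | 16.7 |
| 0.5 | 8.3 |

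A patient on a low rate for several days would be excluded. A patient just started on a rate ten times higher would not be, for the first 8.3 hours. At a daily screen the criterion would measure duration as much as current instability.

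**2. Candidate rate readings at 70 kg.**

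| Reading | Calculation | mg/h |
|---|---|---|
| 0.25 microg/kg/min | 0.25 × 70 × 60 / 1000 | 1.05 |
| 0.25 mg/kg/h (= 250/60 = 4.17 microg/kg/min) | 0.25 × 70 | 17.5 |
| 0.25 mg/kg/min | 0.25 × 70 × 60 | 1050 |

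The readings span 1050 / 1.05 = 1000. Adding only a per-minute term to the printed text would give the highest of them, so the mass unit has to be confirmed along with the time unit. The article does not say which reading was intended.

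**3. The plan's own statistical figure.** p = 50/200 = 0.25. The 95% half-width is 1.96 × √(0.25 × 0.75 / 200) = 0.060, so the interval is 0.190 to 0.310 and the width is 0.120. This agrees with the stated 0.12.

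**4. Effect on the recruitment proportion.** Suppose the unclear limit moves 2 to 20 patients (1% to 10% of 200) out of or into the eligible pool, with 50 still recruited:

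- Removed: 50/198 = 25.3%; 50/180 = 27.8%.
- Added: 50/202 = 24.8%; 50/220 = 22.7%.

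All four values lie inside 19% to 31%.

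**5. Effect on progression.** The Table 3 green recruitment criterion is more than 0.70 × 50 = 35 participants. It does not use the eligible count and is unaffected.

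**The case against.** The strongest reply is that this is a reporting slip in a condensed article. Staff screen from protocol v2.0 and a screening form, neither of which is shown, and both may print the unit correctly. The word infusion already signals a rate, and the screeners are the research team of a single ICU, who would be unlikely to adopt the extreme readings. Other criteria narrow the risk: patients must be weaning and on a spontaneous mode; high PEEP, high FiO2 and arrhythmia needing intervention are excluded; and device settings are adjusted to tolerance. No inferential result depends on the line, and a later trial would write its own eligibility text.

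Much of this stands. The article does not show that any patient was wrongly screened, and the factor of 1000 measures the range of possible readings, not a likely bedside error. The patient shift used above is an assumption, and even so it shows little effect.

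Two things remain. The article chose to state a numeric threshold and stated it in a unit that does not fit, which is different from leaving a detail to a fuller document. And none of the other safeguards limits vasopressor support. A fault in reading the PDF could turn a micro sign into the letter m, but it would not readily remove a time term from an otherwise intact sentence.

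**Conclusion.** The concern holds. As printed, the noradrenaline limb of the haemodynamic exclusion is not a rate, and nothing in the article repairs it. It should be corrected, because it is a stated safety threshold at entry and the correction costs almost nothing.

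The scope is narrow: one of two limbs of one of 11 exclusions. The arrhythmia limb still works. The defect bears on whether the criterion can be applied, not on bias in the feasibility estimates or on the sample size. The document gives no figure for how many patients might be misclassified. Whether screening in practice was affected cannot be judged without v2.0 and the screening form.

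**What to change.** Check the criterion against protocol v2.0 and the screening form, then restate it with the full rate unit: mass per kilogram per unit time, with both the mass unit and the time unit confirmed. The investigators must say which value is right; it should not be inferred from the article.

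If v2.0 and the form are correct, the cost is a one-line correction to the article. If either has the same defect, the screening log and randomised participants should also be re-checked against the intended limit. Table 1 lists no vasopressor dose, so that check would have to draw on the electronic medical record, which the Data collection section names as the source of baseline data.

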### Randomisation and allocation concealment

Using the online randomisation system ‘Sealed Envelope™’ (that conceals allocation), an ICU research team member will randomise a patient once informed consent/informed advice has been obtained and demographic data collected. Participants will be randomised using a 1:1 allocation to either (A)-control arm (standard care) or (B)-intervention arm (MI-E plus standard care). Blinding of participants, clinicians, and outcome assessors will not be possible due to the nature of the intervention.

#### Study arms

##### A. Control arm (standard care)

Patients will receive standard care in relation to mechanical ventilation, ventilator weaning, rehabilitation, standard physiotherapy techniques such as positioning, manual techniques (percussion, expiratory vibrations, expiratory shakes), manual/ventilator hyperinflation, endotracheal suctioning, and nebulisation. The use of MI-E will not be permitted in the standard care control arm. Respiratory physiotherapy treatments will be individualised to patient need at the discretion of the treating physiotherapist and not protocolised. Decisions to extubate and re-intubate will be at the discretion of the attending physician with reason(s) documented.

##### B. Intervention arm (MI-E plus standard care)

For the intervention arm, we will use the MI-E device, Clearway 2 (Breas Medical Ltd., Stratford-Upon-Avon, Warwickshire, UK). This device is reusable between patients with single-use circuit, filter, and interface (mouthpiece, facemask, and flexible catheter mount).

Whilst intubated, treatment will include a minimum of two MI-E sessions via the endotracheal tube (with cuff inflated) following randomisation and prior to extubation. MI-E settings (mode, pressure, timings, flow) will be individualised to each patient based on patient tolerance, chest expansion, and secretion clearance (as assessed by treating physiotherapist, see supplementary file 2). There will be no minimum/maximum time between MI-E sessions. Following extubation (and up to 48 h), patients will receive MI-E delivered via facemask or mouthpiece up to 2 times each day.

#### Outcomes

Feasibility outcomes are listed in Table 2. Clinical endpoints will be collected to understand the feasibility of their collection informing conduct of a future adequately powered trial and not to conduct hypothesis testing related to causation. Feasibility will be assessed using pre-defined progression criteria (Table 3).

**Table 2 Tab2:** Feasibility outcomes

Feasibility outcome	Measurement detail
Proportion of eligible patients approached, consented, and randomised	Screening log and randomisation records
Proportion of MI-E treatment sessions completed	Case report form
Proportion of recruited patients with all clinical outcomes recorded	Case report form
Frequency of adverse events	Case report form
Attrition (participant withdrawal and loss to follow-up)	Case report form and withdrawal records
Acceptability of intervention and trial processes to participants and clinicians	Qualitative interviews Acceptability of intervention measure (AIM)/intervention appropriateness measure (IAM)/feasibility of intervention measure (FIM)
Acceptability of outcome measures to participants and clinicians	Qualitative interviews

**Table 3 Tab3:** Progression criteria (based on feasibility parameters)

	**Summary**	**Action required**
Go (green)	**Recruitment**: > 70% expected recruitment target **Follow-up**: > 75% data completeness **Adherence**: > 75% adherence to intervention	Feasible to continue to main trial
Amend (amber)	**Recruitment:** 50–70% of expected recruitment target **Follow-up**: 65–75% data completeness **Adherence**: 65–75% adherence to intervention	Identify remediable factors; discuss with trial management group
Stop (red)	**Recruitment**: < 50% of expected recruitment target **Follow-up**: < 65% data completeness **Adherence**: < 65% adherence to intervention	Do not progress to main trial, unless there is a strong case that unanticipated remediable factors have been identified

